### Statistical analysis

2.4

SPSS Sample Power version 3.0 (IBM, Armonk, NY) is applied to analyze data. Afterward, all the data are expressed with appropriate characteristics such as mean, median, standard deviation as well as percentage. Continuous and categorical variables are analyzed using χ^2^-tests and independent t-tests, respectively. Intention to treat analysis is applied to evaluate the outcomes. Significant level: *P* < .05.

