## Introduction

1

Pyogenic vertebral osteomyelitis (PVO) is common in acute osteomyelitis over 55 years old.^[1]^ The incidence rate of PVO in high income countries has increased gradually, increasing from 4 to 10 people in each 100 thousand population.^[2,3]^ Patients with PVO often present with nervous system damage, persistent infection and distortion.^[4,5]^ If the patient is diagnosed with early PVO, conservative treatment can obtain good results.^[6,7]^ However, patients with progressive physical instability pain, epidural abscesses, neurological damage, and antibiotic failure often need surgical operation. More and more surgeons realize that surgical treatment and fixation can reduce pain, improve spinal balance and neurologic, and lead to initial ambulation.

This paper introduces the different results of anterior minimally invasive retroperitoneal oblique approach (ORA) and posterior transpedicular approach (PTA) debridement. The ORA has the following advantages, such as less impact on nervous system, and relatively consistent access to the lower lumbar levels.^[8]^ However, in some cases involving high riding pelvis, access to the lower lumbar level is limited. Therefore, in order to perform lumbar interbody fusion from L1 to S1, the surgeon needs to separate the incision or change the position. PTA surgery is gradually accepted by surgeons. Some surgeons claimed that single-stage debridement and instrumented interbody fusion can eliminate local diseases, reduce nerve pressure, and rectify spinal malformation in single-stage surgery with smaller trauma, fewer complications, lower cost and shorter rehabilitation time.^[9,10]^ While the best treatment of PVO is still controversial, and there are few reports about it. The aim of the protocol is to compare the clinical outcomes between PTA and ORA for treating PVO.

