## Materials and methods

2

The experiment will be implemented from December 2020 to December 2021 at the People's Hospital of Dayi County, in accordance with the purposes of the Declaration of Helsinki. The experiment was admitted by the Research Ethics Committee of the People's Hospital of Dayi County (Approval number: 1002-084) and recorded in research registry (Identifier: researchregistry6046). The experiment is a single-center randomized clinical research. The recruited patients provide written informed consent prior to enrollment.

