### Inclusion and exclusion criteria

2.1

In all, 50 patients with lumbar vertebral osteomyelitis (LVO) who prepares surgical treatment will be included in the study. We include adult patients (aged above 18 years) who accept debridement and spinal stabilization with LVO. LVO has three characteristics: symptoms (back pain, fever and reduced lumbar range of motion), X-ray (vertebral and intervertebral disc lesions), and bacterial pathogens (confirmed by laboratory tests). All patients have intact medical reports. Cases are removed if there is previous hardware placement, cases who are not confirmed by microbiology, or severe renal and liver dysfunction. All patients are followed up for at least 12 months.

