### Outcomes

2.3

The primary outcomes are intraoperative blood loss, operative time, hospital stay, primary failure and recurrence, and bone fusion. The secondary outcomes are postoperative pain score and physical recovery. Patient Reported Outcomes Measurement Information System^[11]^ are used to evaluate physical function.

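### Operative time and blood loss are to be compared without adjustment in 50 patients; prespecifying preoperative disease extent as a covariate would be a cheap gain in precision if extent is prognostic

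*Protocol article*

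**What the plan says.** Section 2.4 (Statistical analysis) lists two tests, chi-square and "independent t-tests, respectively", at P < .05 under intention to treat. It names no covariate, stratification factor or regression model. Read literally, the sentence pairs chi-square tests with continuous variables and t-tests with categorical ones.

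Section 2.3 (Outcomes) states: "The primary outcomes are intraoperative blood loss, operative time, hospital stay, primary failure and recurrence, and bone fusion". Blood loss, operative time and hospital stay are continuous.

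Section 2 describes the design: "The experiment is a single-center randomized clinical research". Section 2.1 gives the size: "In all, 50 patients with lumbar vertebral osteomyelitis (LVO) who prepares surgical treatment will be included in the study". The article states no allocation ratio, effect size, standard deviation (SD) or power.

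Section 2.1 also makes imaging part of the case definition: "X-ray (vertebral and intervertebral disc lesions". Its exclusions are earlier hardware, lack of microbiological confirmation, and severe renal and liver dysfunction. None concerns the number of infected levels. Section 2.2 has debridement in the oblique approach continue until healthy bone is reached. It describes vessel ligation in that approach, bone and disc resection in the posterior approach, and cages and screw fixation.

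**The concern.** Single-level and multi-level disease can both enter the trial. More diseased segments plausibly mean more debridement, resection, cage and fixation work, and so a longer operation with more bleeding. If so, a two-sample t-test leaves that between-patient variation in its error term, and a chance imbalance in multi-segment disease shifts the observed difference between approaches. Across repeated trials such shifts average to zero and the standard error allows for them, but they widen the confidence interval. With 50 patients that width decides how small a difference can be detected.

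Extent before surgery cannot be altered by the approach later used, so adjusting for it is safe, provided it is read from preoperative images without regard to the assigned arm.

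**Working it through.** **The plan's own figure.** The total of 50 cannot be reproduced, because the article gives no effect size, SD, power or allocation ratio. What follows assumes 1:1 allocation (25 per arm) and two-sided alpha 0.05.

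**Step 1. Detectable difference without adjustment.** At 80% power, (1.960 + 0.842) × sqrt(2/25) = 0.79 SD by the normal approximation. The noncentral t distribution gives 0.81 SD.

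**Step 2. Effect of adjustment.** Let R-squared be the share of within-arm outcome variance explained by the covariate as entered in the model. The residual SD is SD × sqrt(1 − R-squared), and the equivalent unadjusted sample size is 50/(1 − R-squared). The power column uses the noncentral t at an assumed true difference of 0.8 SD. Its adjusted rows use 47 degrees of freedom and a variance factor of (1 − R-squared) × (1 + 1/46), which charges for estimating the extra coefficient.

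| R-squared (assumed) | Detectable difference, 80% power (normal approx.) | Equivalent unadjusted N | Power at 0.8 SD |
|---|---|---|---|
| Unadjusted | 0.79 SD | 50 | 79% |
| 0.1 | 0.75 SD | 56 | 82% |
| 0.2 | 0.71 SD | 63 | 87% |
| 0.3 | 0.66 SD | 71 | 91% |
| 0.4 | 0.61 SD | 83 | 94% |

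Applying the 1 + 1/46 factor to the equivalent N as well lowers the ends of the range slightly: 55.6 becomes 54.4 and 83.3 becomes 81.6.

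**Step 3. Break-even and downside.** At R-squared 0.02 the variance factor is 0.98 × 1.022 = 1.00, so there is no gain or loss. At R-squared 0, adjusted power is 78% against 79% unadjusted. A simulation of 10,000 trials gave 78.0% against 79.0%.

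**Step 4. What R-squared might be for operative time.** The article gives no figure, so every input here is an assumption: 40% of patients have multi-segment disease, it adds 40, 60 or 80 min, the SD within each extent group is 50 min, and the true difference between approaches is 40 min. The variance due to extent is 0.4 × 0.6 × (added time)².

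| Added time | Variance from extent | Total SD | R-squared | Difference in SD units | Power unadjusted | Power adjusted |
|---|---|---|---|---|---|---|
| 40 min | 384 | sqrt(2884) = 53.7 | 0.13 | 0.75 | 0.73 | 0.78 |
| 60 min | 864 | sqrt(3364) = 58.0 | 0.26 | 0.69 | 0.66 | 0.78 |
| 80 min | 1536 | sqrt(4036) = 63.5 | 0.38 | 0.63 | 0.58 | 0.78 |

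The powers are from simulation (8,000 trials per case). Unadjusted powers from the noncentral t agree within 0.01 (0.73, 0.67, 0.59). Type I error was 0.050–0.053 unadjusted and 0.052–0.054 adjusted. The smallest case is worth 50/(1 − 0.133) = 58 patients. Varying the multi-segment share from 30% to 50% moves R-squared only to 0.12–0.14 for 40 min added and 0.35–0.39 for 80 min added.

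**Step 5. Chance imbalance.** With two independent binomial counts out of 25, the arms differ by 5 or more multi-segment patients with probability 0.16, 0.19 and 0.20 for shares of 30%, 40% and 50%. An imbalance of exactly 5 shifts the unadjusted difference by 5/25 × 40 to 80 min = 8 to 16 min.

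No calculation on the original scale was made for blood loss. For that outcome only the R-squared table applies.

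**The case against.** The strongest objection is that nothing here is wrong. An unadjusted comparison is a legitimate primary analysis of a randomised trial, its type I error is held, and covariates are often fixed in an analysis plan that is not shown. Most of this stands: the loss is one of efficiency, and it does not invalidate the result. It does not dispose of the point, because section 2.4 does not leave the method open. It names the tests, and a better method is available at almost no cost.

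Second, the quoted sentence literally assigns t-tests to categorical variables, so the criticism applies to a repaired sentence. This is true. The swap is the plainer error and must be corrected first, but the corrected sentence is still unadjusted.

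Third, a reader might infer more than the article supports:

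- That the number of segments is shown to drive operative time and blood loss. No section says so; the link is a clinical inference from the surgical steps in section 2.2.
- That the number of segments is already recorded and known before randomisation. Section 2.1 requires lesions on imaging but does not say that segments are counted, and the article does not place imaging relative to allocation.
- That the Introduction establishes multi-segment disease in this trial. Its words "in order to perform lumbar interbody fusion from L1 to S1" concern access by the oblique approach when the pelvis rides high. They do not describe how many segments are infected.
- That an imbalance in extent biases the comparison. Under randomisation it is chance variation that the standard error already covers.
- That hospital stay gains in the same way. No argument or calculation supports that.

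Finally, other covariates could be chosen, and the article does not single out segment count. That also stands. Segment count is proposed because it can be read from existing images and relates to the amount of surgery.

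**Conclusion.** The point holds as a conditional one about efficiency. After the test names are put right, section 2.4 compares operative time and blood loss by a valid but unadjusted t-test in 50 patients, and so leaves unused a baseline variable that can be read from the required imaging and is likely to be prognostic. If extent explains 10% to 40% of within-arm variance, adjustment is worth about 56 to 83 unadjusted patients. If it explains less than about 2%, nothing is gained, and at zero about one percentage point of power is lost. These figures rest on 25 patients per arm, two-sided alpha 0.05 and an assumed R-squared; the article supplies none of the three in full. It is a cheap improvement of low to moderate priority.

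**What to change.** In section 2.4, first match the tests to the variable types. Then state that operative time and blood loss are compared by linear regression on randomised arm, with the number of infected segments on preoperative imaging (one versus two or more) as a prespecified covariate. Report the adjusted mean difference with its 95% confidence interval, and keep the unadjusted comparison as supportive.

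Add segment count to the baseline variables, recorded from the preoperative images independently of the assigned approach.

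The cost is one degree of freedom, a few words of protocol text and abstraction of one variable from images that already exist. It needs no extra visits or patients.

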## Results

3

Table 1 will show the outcomes in both groups.

**Table 1 T1:**
[figure not shown]
Comparison of clinical outcomes after operation.

## Discussion

4

Many PVO patients can only use a certain amount of antibiotics. With the rapid development of neurological complications, surgical treatment is needed.^[12]^ With the continuous progress of minimally invasive method, oblique lumbar interbody fusion and lateral lumbar interbody fusion have become the option of spine surgeons.^[13,14]^ Minimally invasive ORA can directly enter the infected lesions, which is convenient for debridement.^[15,16]^ The debridement time is shorter that the amount of bleeding during operation is easy to control. In addition, the trauma to patients can be controlled through channels and microscope systems. However, thorough debridement is the central technique for the treatment of PVO. Percutaneous pedicle screws are effective for ventral decompression,^[17]^ but there are some difficulties in posterior decompression, and it is laborious to eliminate abscesses in the contralateral psoas major. Moreover, PTA can enter the infection indirectly, but it may be better than ORA in posterior decompression. Currently, no reliable evidence regarding the optimal approaches has been reported in PVO. Further investigation with large sample sizes is required.

## Conclusion

5

This protocol may offer a reliable basis for the effectiveness of the two approaches in the treatment of PVO.
